## Outcome assessment

We will use the Claim Evaluation Tools as the outcome measure, as applied at the level of individual children. The Claim Evaluation Tools consist of multiple choice items that assess an individual’s ability to apply 32 concepts that people must be able to understand and apply to assess treatment claims and to make informed health care choices [34]. The Claim Evaluation Tools have been developed based on extensive qualitative and quantitative feedback from methodological experts, health professionals, teachers and members of the public [34].

The questionnaires have also been subject to psychometric testing including Rasch analysis on two occasions. The first test comprised a diverse sample of over 1000 people including primary-five children exposed to pilot versions of the IHC school resources, children who were not exposed, and adults with very little or no exposure and adults who are familiar with the concepts [35]. Questions covering 24 of the 32 concepts were administered as written questionnaires in English. In this test, the items were found to have high reliability (Cronbach’s alpha = 0.81), and to be unidimensional (that is, there was no evidence of subdimensions measuring different traits). Furthermore, there was weak or no dependence among items (that is, no items were found to be redundant). Children who participated in the pilot scored better than other children, and most of the questions did not over- or under-discriminate or function differently across subgroups of participants. However, some of the questions were too difficult, particularly for children with poor reading skills.

After removing some questions, we modified the remaining questions that did not perform well according to the Rasch analysis, and revised and simplified the text where needed. The items were also translated to Luganda and adapted for audio administration. In the second psychometric testing, the Claim Evaluation Tools were administered to a similar sample as described in the first psychometric test, but approximately half of the sample received the items as a written questionnaire in English and the other half received the Luganda audio versions. The results of this test suggested that the items administered in English performed very well according to the Rasch model, and with high reliability. Furthermore, the items were also less difficult than what was found in the first psychometric testing before the revisions. The results also suggested that the Luganda versions of items had evidence of under-discrimination and differential item functioning in seven out of 29 items. These items were revised to improve fit to the Rasch model.

Based on these two psychometric tests, a selection of 24 multiple choice items addressing the 12 concepts that the IHC primary school resources cover will be used (see: Additional file 1). Each key concept is evaluated by two items. We chose items with high reliability (fit to the Rasch model) and those with an appropriate difficulty level.

The Claim Evaluation Tools also include items that assess intended behaviours, self-efficacy and attitudes associated with assessing claims and finding evidence, as well as items assessing satisfaction with the intervention relevant for primary school children (see: Additional file 1). In addition, we have included four questions that assess literacy, which we will use as a covariate in exploratory analyses, and questions about attitudes towards school. We will also compare attendance and academic achievement (using end-of-term examinations) between children in the two comparison groups.

Children in both arms of the trial will complete the questionnaire in their classrooms at the end of the term. Research assistants will ensure that the questionnaires are delivered on time, that the children are given one full hour to answer the questions, as is current practice for primary school exams in Uganda, and that the questionnaires are collected and returned to the study investigators.

### Absolute standard (for passing scores)

We will use an absolute (criterion referenced) standard to set a passing score for the version of the Claim Evaluation Tools that we will use; i.e. based on how much the children know and are able to apply. Children will be counted as ‘passing’ or ‘failing’ depending on whether they meet a specified criterion. We used a combination of Nedelsky’s and Angoff’s methods to determine the criterion [36–38], which is a cut-off for a passing score, as described in Additional file 2. In addition, we determined a second cut-off for a score that indicates mastery of the 12 concepts, using the same methods, as described in Additional file 2. The criterion for passing is a minimum of 13 out of 24 questions answered correctly. The criterion for mastery is a minimum of 20 out of 24 questions answered correctly.

To enable a sensitivity analysis, we will administer the Claim Evaluation Tools verbally to a sample of children at each school to enable estimation of the impact that literacy might have on the scores that the children achieve on the written version.

### Primary outcomes

The difference between the intervention and control groups in the proportion of children with a *passing* score (see above)The mean difference in the score (number of correct answers) for all of the questions that assess their ability to apply the 12 concepts that are included in the IHC primary school resources

### Secondary outcomes

The mean difference and the difference between the intervention and control groups in the proportion of children with a passing score for a subgroup of children to whom the Claim Evaluation Tool will be administered orallyThe difference between the intervention and control groups in the proportion of children with a score indicating *mastery* of the concepts (see above)The difference between the intervention and control groups for each concept and for the questions intended to measure their understanding of the conceptsDifferences in intended behaviours and self-efficacy (see: Additional file 1)Differences in attitudes towards science and school (see: Additional file 1)Differences in attendance and academic achievement as indicated by school marks

We will ask the participating schools to provide us with school attendance records and summary score sheets containing all pupils’ end-of-term examination scores. The summary score sheet contains percentage scores for each end-of-term examination, each pupil’s position in class, and a total score aggregated across subjects (Table 6). The children receive marks for English, mathematics, social studies and science. We will measure the mean difference between the intervention and control groups for each subject and for their total score (points awarded).

**Table 6 Tab6:** Ranges of marks and points awarded for each subject

Exam score (out of 100)	Points awarded	Marks
80–100	1	Distinction 1
70–79	2	Distinction 2
65–69	3	Credit 3
60–64	4	Credit 4
55–59	5	Credit 5
50–54	6	Credit 6
45–49	7	Pass 7
35–44	8	Pass 8
Below 35	9	Failure

We will measure all of the above outcomes again after 1 year.

## Blinding

The comparison will not be blinded. All of the participants in the trial will be informed of the purpose of the study and will know whether they are in the intervention or control arm. The head teachers and the district education officers will be informed of the purpose of the study when they are recruited. The primary-five teachers in both arms of the trial will be informed of the purpose of the study prior to the delivery of the intervention. Children in both arms of the trial will be informed of the purpose of the Claim Evaluation Tools when they are asked to complete them. They will also be asked to put their names on the questionnaires and will be told that they and their teachers will be told their scores.

## Data collection and management

We will ask the primary-five teachers to complete a brief form at the beginning of the term to collect baseline data about the teachers in both arms of the trial (see: Additional file 3). This will include their age, gender, level of education, number of years teaching, and subjects taught. Research assistants will collect missing information by contacting the teachers by telephone or visiting the schools.

Two research assistants will independently enter data from these forms and the Claim Evaluation Tools into a database using EpiData [39]. To reduce the number of unclear or missing values, the research assistants will check all the questionnaires at the schools when they collect them and clarify any unclear entries immediately.

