## Analysis

For the primary and secondary outcomes, we will use mixed models with a random effects term for the clusters and the stratification variables modelled as fixed effects, using logistic regression for dichotomous outcomes, linear regression for continuous outcomes and Poisson regression for count outcomes. For the questions that assess applied knowledge or understanding, missing values will be counted as wrong answers.

For each outcome, we will report the proportion, mean and standard deviation, or median and interquartile range for each group, the estimated difference, the estimated confidence interval for the difference, and the *p* value from the statistical model. For questions about intended behaviours and self-efficacy (see: Additional file 1), we will dichotomise the responses (e.g. ‘very unlikely or unlikely’ versus ‘very likely or likely’) in the analysis and we will report the proportions of children for each of the four response options.

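### The on-site check of completed questionnaires does not exempt the 24 scored items, which leaves an avoidable opening for differential bias in both primary outcomes of an open trial

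*Protocol article*

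**What the plan says.** All references are to the protocol article.

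- **Data collection and management.** The purpose of the check is given as "To reduce the number of unclear or missing values". The action is that "the research assistants will check all the questionnaires at the schools when they collect them and clarify any unclear entries immediately". The sentence before it names the Claim Evaluation Tools among the forms handled, and no part of the questionnaire is excepted. Two research assistants then enter the data independently.
- **Analysis.** For the questions on applied knowledge or understanding, "missing values will be counted as wrong answers".
- **Absolute standard (for passing scores).** "The criterion for passing is a minimum of 13 out of 24 questions answered correctly".
- **Primary outcomes.** The first is the difference in the proportion passing. The second is "The mean difference in the score (number of correct answers) for all of the questions" on the 12 concepts. Both are computed from the same 24 answers.
- **Blinding.** "The comparison will not be blinded". Of the children it says: "They will also be asked to put their names on the questionnaires". No blinded role is described for anyone.
- **Outcome assessment.** The test is taken in the classroom at the end of term, and research assistants ensure that "the children are given one full hour to answer the questions".

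**The concern.** Multiple-choice scoring is objective once the mark on the paper is fixed. The weak point is the interval between the child putting the pencil down and the mark being treated as final. In that interval the plan has staff look over every paper and settle what is unclear, with the declared aim of having fewer missing values.

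Two rules then pull against each other. The analysis treats a blank on a scored item as a result, namely wrong. The field procedure aims to have fewer blanks before that rule is applied. For such an item, follow-up works in one direction only: the score stays the same or goes up.

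The staff involved probably know the arm. The trial is open, they work inside the school, and according to the section on the textbook, exercise books and reminders, intervention schools receive a checklist poster for the classroom. If effort or wording at this step differed between arms, both primary outcomes would carry the difference. Double data entry comes after the check, so it cannot show what was on the paper beforehand.

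**Working it through.** **1. The plan's own figures, used here only as yardsticks.** Inputs from Sample size: 0% against 10% passing, alpha 0.05 (taken as two-sided), power 90%, 70 children per school, ICC 0.5.

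- Per arm without clustering: n = [1.96 × √(2 × 0.05 × 0.95) + 1.2816 × √(0 + 0.10 × 0.90)]² / 0.10² = (0.604 + 0.384)² / 0.01 ≈ 97.7, so 98.
- Design effect: 1 + (70 − 1) × 0.5 = 35.5.
- Schools per arm: 98 × 35.5 / 70 = 49.7, so 50. Then 50 × 1.10 = 55.

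The stated 50 and 55 reproduce. The yardsticks are therefore 10 percentage points for passing and one correct answer for the score. The point made here is procedural and does not depend on the sample size. More schools would not remove a systematic difference between arms.

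**2. Direction of the effect on one scored item.**

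| State of the item at collection | Score if left alone | Score after an on-site query | Possible change |
|---|---|---|---|
| Blank | 0 (Analysis) | 0 or 1 | none or up |
| Unclear or double mark | not stated in the article | 0 or 1 | depends on how it is settled, and by whom |

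**3. Shift in the mean score.** Let d be the extra items per child filled in one arm over the other, and g the chance that a filled item is correct. The shift is d × g. The article gives neither. Assumptions: d from 0 to 2, and g from 0.25 to 0.33 (a pure guess among four or three options; the number of options is assumed).

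| d | g = 0.25 | g = 0.33 (one in three) |
|---|---|---|
| 0 | 0 | 0 |
| 1 | 0.25 | 0.33 |
| 2 | 0.50 | 0.67 |

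Reaching the one-answer yardstick by guessing alone would need d = 1/0.25 = 4 or d = 1/0.33 ≈ 3 extra items per child. A child who partly knew the answer would have a higher g; at g = 0.5, two items add 1.0.

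**4. Shift in the pass rate.** Assume 24 independent items with a common chance p of a correct answer. A child who gains one correct answer passes with 12 instead of 13, so the gain is P(X ≥ 12) − P(X ≥ 13).

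| p | P(X ≥ 13) | P(X ≥ 12) | Gain if every child in one arm gains one answer | Gain if a quarter do |
|---|---|---|---|---|
| 0.40 | 11.4% | 21.3% | 9.9 points | 2.5 points |
| 0.50 | 41.9% | 58.1% | 16.1 points | 4.0 points |

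The row p = 0.40 lies near the 10% pass rate that the sample size supposes in the intervention arm. The case in which every child gains an answer is an outer bound for illustration, not a forecast.

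**5. Condition for bias.** If d is zero, the shift between arms in steps 3 and 4 is zero. If d is not zero, the sign depends on which arm received more follow-up, and the article does not settle that.

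**The case against.** The case on the other side is substantial, and much of it stands.

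- **The action covers unclear entries, not blanks.** Missing values appear only in the purpose clause. A reader might infer that assistants go back to children and have blanks filled in. The article does not say so. The questionnaire also holds the name and items on intentions, self-efficacy and attitudes, where the blank-equals-wrong rule does not apply and where a check has ordinary value. That rule also presupposes that some scored blanks survive collection.
- **The hour.** A reader might infer that answers are added after time is up. The text only guarantees children a full hour and does not describe late answers.
- **Knowledge of arm.** The Blinding section lists who is told the purpose and does not mention research assistants. That they know the arm is a fair inference from an open trial, but it is an inference.
- **Both arms get the same check.** Equal handling produces no difference between arms, and no mechanism for unequal handling is stated.
- **The upper illustration is demanding.** Two extra items for each of 70 children is 140 items per school, or 7,700 across 55 schools, over and above the other arm.
- **Field detail.** Scripts and change logs belong in a manual, and their absence from an article is no fault.

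What remains is the sentence as printed. It covers all questionnaires, aims at fewer missing values, and makes no exception for the items that form the primary outcomes. That is a stated procedure, not an omitted detail.

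**Conclusion.** The point holds as a weakness in a stated procedure. In an open trial, staff who probably know the arm check completed papers and settle unclear entries. The 24 scored items are within the scope of that check, and any blank completed through it can only keep or raise the score.

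The document does not support the claim that staff will raise scores in one arm, or that blanks will be filled at all. The opening for differential bias is real, but its use and its direction are unknown. Its size cannot be derived. On the assumptions shown, the mean shift runs from 0 to about 0.67 answers against a one-answer difference of interest. If a quarter of the children in one arm gained one answer, the pass rate would move by 2.5 to 4.0 points against a 10-point difference. Zero is within the range.

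The change is worth making because it costs almost nothing and protects both primary outcomes. It is not a reason to doubt the design as a whole.

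**What to change.** Amend the data-collection procedure as follows.

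1. Limit on-site checks to identifiers and non-scored items.
2. State that the 24 scored items stay as the child left them and are not queried, completed or altered after collection.
3. Code double-marked or illegible answers on those items by one fixed rule at data entry, applied by staff who work from school codes without the arm. Random allocation already gives each school a study code.
4. Report the number of blank and of ambiguous answers by arm.

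**Cost.** One or two sentences in the procedure, the matching instruction in assistant training, and a short table in the report. Slightly more ambiguous answers will be scored wrong, some of which a child could have clarified. That loss need not be exactly equal in the two arms, which is why step 4 is part of the change.

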## Analysis

For the primary and secondary outcomes, we will use mixed models with a random effects term for the clusters and the stratification variables modelled as fixed effects, using logistic regression for dichotomous outcomes, linear regression for continuous outcomes and Poisson regression for count outcomes. For the questions that assess applied knowledge or understanding, missing values will be counted as wrong answers.

For each outcome, we will report the proportion, mean and standard deviation, or median and interquartile range for each group, the estimated difference, the estimated confidence interval for the difference, and the *p* value from the statistical model. For questions about intended behaviours and self-efficacy (see: Additional file 1), we will dichotomise the responses (e.g. ‘very unlikely or unlikely’ versus ‘very likely or likely’) in the analysis and we will report the proportions of children for each of the four response options.

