**Methods:**

This is a two-arm, cluster-randomised trial with stratified random allocation. We will recruit 120 primary schools (the clusters) between April and May 2016 in the central region of Uganda. We will stratify participating schools by geographical setting (rural, semi-urban, or urban) and ownership (public or private).

The Informed Healthcare Choices (IHC) primary school resources consist of a textbook and a teachers’ guide. Each of the students in the intervention arm will receive a textbook and attend nine lessons delivered by their teachers during a school term, with each lesson lasting 80 min. The lessons cover 12 key concepts that are relevant to assessing claims about treatments and making informed health care choices. The second arm will carry on with the current primary school curriculum.

We have designed the Claim Evaluation Tools to measure people’s ability to apply key concepts related to assessing claims about the effects of treatments and making informed health care choices. The Claim Evaluation Tools use multiple choice questions addressing each of the 12 concepts covered by the IHC school resources. Using the Claim Evaluation Tools we will measure two primary outcomes: (1) the proportion of children who ‘pass’, based on an absolute standard and (2) their average scores.

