### Random allocation

Schools will form the basic units (clusters) for allocation. Each school will be numbered and listed, and the study arm allocation will be determined using computer-generated randomisation, with equal numbers of the schools allocated to each arm in each stratum.

A statistician who is not a member of the research team will use computer-generated allocation sequences (www.sealedenvelope.com) to randomly allocate schools to either the control or intervention arm. No changes to allocation will be made subsequent to this.

We will use a block size of 4, with equal allocation ratios in each block and strata. The lists for each district will be randomly generated as shown in the table below (Table 1).

**Table 1 Tab1:** Examples of random allocation sequence

Block identifier	Block size	Sequence within block	Treatment	Location	Ownership	Code
1	4	1	Group A	Rural	Government	FZ4
1	4	2	Group A	Rural	Government	MG9
1	4	3	Group B	Rural	Government	NC5
1	4	4	Group B	Rural	Government	ID9
2	4	1	Group B	Rural	Government	VO9
2	4	2	Group B	Rural	Government	UA4
2	4	3	Group A	Rural	Government	KB5
2	4	4	Group A	Rural	Government	OQ6

As shown above (Table 1), the statistician will prepare a randomisation list with unique codes and corresponding allocation groups for each participating school. We will prepare separate lists for each stratum; i.e. rural-government for a rural school owned by government, rural-private for a rural school owned privately; suburban-private for a suburban school that is owned privately, suburban-government for a suburban school that is owned by government, urban-private for an urban school owned privately, and urban-government for an urban school that is government owned. These will contain only the participant school’s study code. Study allocation groups (intervention or control) corresponding to each study code will be inserted in envelopes and sealed. Every envelope will contain its study code as a label. For example, if the school is located in a rural area and it is a government school, a list will be prepared from the general list for that particular district. Below is an example of the study groups with corresponding study codes (Table 2).

**Table 2 Tab2:** Example of study groups and corresponding study codes

Treatment	Code
Group A	FZ4
Group A	MG9
Group B	NC5

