## Sample size

We used the University of Aberdeen Health Services Research Unit’s Cluster Sample Size Calculator [42] to calculate the sample size with the following assumptions:Children per cluster = 70Intraclass correlation coefficient (ICC) = 0.5, based on ICCs from a meta-analysis of randomised trials of school effectiveness which found ICCs to be higher than those reported for test scores in the USA [43]The proportion of children expected to achieve a passing score without the intervention, based on findings from pilot testing = 0%The smallest difference we want to be able to detect = 10%Alpha = 0.05Power = 90%

Based on these assumptions, we would need a total of 50 schools in each arm for the study to have 90% power to detect a difference of 10% between the two groups. Allowing for a loss to follow-up of up to 10% (for schools where it is not possible to administer the Claim Evaluation Tools at the end of the term), we estimate that we need a minimum of 55 schools in each group. This would provide more than 90% power to detect a mean improvement of one more correct answer for the 12 concepts covered by the primary school resources.

More specific information about the trial and the protocol is summarised in the Standard Protocol Items: Recommendations for Interventional Trials (SPIRIT) Checklist (see: Additional file 4).

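### The models are valid but leave precision unused: a prior-term school exam mean would be a cheap covariate for the mean score, and prior-term values for school marks and attendance

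*Protocol article*

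**What the plan says.** The Analysis section covers the primary and secondary outcomes together: "mixed models with a random effects term for the clusters and the stratification variables modelled as fixed effects", with a logistic, linear or Poisson form according to the type of outcome. The stratification variables are setting (three levels) and ownership (two levels), and Random allocation provides for "equal numbers of the schools allocated to each arm in each stratum".

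No measure of the children's attainment before the intervention is described. Data collection and management lists baseline data on teachers only. Four literacy questions are named under Outcome assessment as a covariate, but for exploratory analyses, and they sit on the end-of-term questionnaire, so they are answered after the intervention.

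Under Secondary outcomes the authors write: "We will ask the participating schools to provide us with school attendance records and summary score sheets containing all pupils’ end-of-term examination scores". These records supply the attendance and academic-achievement outcomes for the trial term, to be measured again after one year. Records from the term before the intervention are not mentioned.

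The Sample size section plans with 70 children per school and an ICC of 0.5.

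**The concern.** When the ICC is as high as 0.5, the precision of the arm comparison depends almost wholly on how much schools differ from one another. Testing more children in each school hardly helps. Apart from adding schools, the remaining lever is to explain part of the between-school variation with something measured before the intervention. Prior school attainment is a natural candidate, and the model omits it.

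What is at stake is the width of the confidence interval for the mean-score primary outcome and for the comparisons of marks and attendance. For marks and attendance the covariate would be the same measure one term earlier. Validity is not at stake: schools are randomised within strata, so differences in level before the trial add noise but no bias.

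**Working it through.** **Inputs from the protocol article.** Sample size: 70 children per school; ICC 0.5; 0% passing expected in controls; detectable difference 10 percentage points; alpha 0.05; power 90%; 10% loss of schools. Abstract: 120 schools to be recruited, or 60 per arm.

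**Input not in the article (assumption).** R², the share of the between-school variance remaining after setting and ownership that the prior exam mean explains. Values of 0.10, 0.25, 0.36 and 0.50 are shown. The last three correspond to school-level correlations of 0.5, 0.6 and about 0.7.

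**Step 1: the plan's own figure.** Two proportions, 0 versus 0.10, two-sided (sidedness is not stated), no continuity correction:

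n = [1.96·√(2·0.05·0.95) + 1.2816·√(0.10·0.90)]² / 0.10² = (0.604 + 0.384)² / 0.01, or 98 children per arm before clustering.

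Design effect = 1 + (70 − 1)·0.5 = 35.5.

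Schools per arm = 98·35.5/70 = 49.7, so 50. This matches the stated 50. Dividing by 0.9 for loss gives 55.6, against the stated 55. Unadjusted power for the pass outcome is 90% at 50 schools per arm, 93% at 55 and 95% at 60.

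**Step 2: where the variance of a school mean lies.** With total variance set to 1:

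Var = ICC + (1 − ICC)/70 = 0.5 + 0.5/70 = 0.5071

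Between-school share = 0.5/0.5071 = 98.6%.

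Doubling to 140 children per school gives 0.5 + 0.5/140 = 0.5036, a fall of 0.7%.

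**Step 3: effect of a school-level covariate on a continuous outcome.** Var(R²) = 0.5·(1 − R²) + 0.5/70. The SE ratio is the square root of Var(R²)/0.5071.

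| Assumed R² | Var(R²) | Variance ratio | SE ratio | Fall in SE | 50 schools per arm act like |
|---|---|---|---|---|---|
| 0.10 | 0.4571 | 0.901 | 0.949 | 5% | 55 |
| 0.25 | 0.3821 | 0.754 | 0.868 | 13% | 66 |
| 0.36 | 0.3271 | 0.645 | 0.803 | 20% | 78 |
| 0.50 | 0.2571 | 0.507 | 0.712 | 29% | 99 |

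The last column is 50 divided by the variance ratio.

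The formula treats 0.5 as the between-school variance left after the strata. If setting and ownership already remove part of it, the within-school term (0.5/70 = 0.007) is still small, so the SE ratio stays close to √(1 − R²). The percentages hold as long as R² is counted beyond the strata.

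**The case against.** The strongest reply is that nothing here is an error. The model follows the stratified design, is unbiased, and already adjusts for two plausible correlates of school attainment. That stands: the point is about efficiency.

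The reply continues that further covariates may be set out in a statistical analysis plan that is not shown. The Analysis section does state the model and its fixed effects, so the point concerns a stated choice. If a fuller plan adds prior attainment, and the prior-term records are collected, the point falls away.

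A third reply is that the size of the gain is unknown. The article does not say that prior-term sheets are kept by every school, or that exams are common across schools. If each school sets or marks its own papers, school means may say little about ability and R² may be near zero. This also stands, which is why the range starts low. Little is lost in that case: one or two degrees of freedom among about 120 schools.

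A reader might also think the data are already in hand because schools will supply score sheets. Those sheets are for the trial term, and they are outcomes measured after the intervention. The prior-term sheet is the same type of record but needs a further request.

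**Conclusion.** The point holds as a cheap improvement to a valid analysis. Under the protocol's own ICC and cluster size, 98.6% of the variance of a school mean is between schools. A prespecified pre-intervention school covariate would reduce the SE for continuous outcomes by about 5% to 29% for an assumed R² of 0.10 to 0.50 beyond the strata, and by close to nothing if exam marks are not comparable. The calculation applies the planning ICC to these outcomes and uses linear models. If attendance is analysed as a count, the figures are only a guide.

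Three stronger readings are not supported:

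- **That the trial has well under its stated 90% power.** For the pass outcome, 50 schools per arm reproduces. For one more correct answer on the mean score, no standard deviation is given, so low power cannot be shown from this document. With ICC 0.5, 90% power needs a total SD of at most 2.17, 2.27 or 2.37 at 50, 55 or 60 schools per arm. Whether that is realistic is a separate sample-size question.
- **That the comparison is unadjusted and gives away most of the attainable precision.** It is adjusted for the strata, and even R² of 0.50 cuts the SE by 29%.
- **That both primary outcomes gain.** With 0% expected to pass in control schools, there is little control-arm variation between schools to explain. In a logistic model an added covariate also changes the conditional odds ratio, so the linear formula does not carry over.

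**What to change.** - When asking schools for attendance records and end-of-term score sheets, also ask for the sheet and attendance record of the term before the intervention, in both arms and in the same way.
- Prespecify the school-mean prior exam mark (for example, English and science) as a fixed effect in the mean-score primary model, alongside the stratification variables.
- In the models for marks and attendance, prespecify the prior-term value of the same measure.
- For a school without a sheet, impute the stratum mean and add a missing indicator, so that no school is dropped.
- Leave the pass model as stated unless a gain is shown for it separately.

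The cost is one additional record request per school (about 120 school-level values for the mean-score covariate), minor data entry, and some missing sheets. Research assistants are already due to telephone or visit schools for missing teacher information, so the route exists.
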